In the Netherlands, patients are eligible for CRS-HIPEC if the PCI does not exceed 20 at surgical exploration [21]. All participating centers perform CRS-HIPEC procedures under the Dutch HIPEC protocol, as described by Kuijpers and colleagues [21]. With this policy in mind, the cut-off points for MRI-assessment have been determined using preliminary data of the initiating center [15]. The MRI-PCI cut-off of 15 ensures targeted use of DLS and the cut-off of 24 prevents the false omission of patients for whom CRS-HIPEC is feasible. If a specific disease localization is found which could contraindicate CRS-HIPEC, i.e. duodenal involvement, DLS may still be performed at the discretion of the multidisciplinary team (MDT). Surgical procedures must be performed within 4 weeks after the MRI.

In arm B, patients undergo the standard diagnostic work-up followed by a DLS at the discretion of the MDT, as determined before randomization. For the control group no study specific guidelines for DLS use have been determined, centers are expected to continue implementing DLS according to their own current policies. The rate of laparoscopy use may therefore vary between centers.

All patients will be asked to fill in two QOL questionnaires (EORTC-C30 and EQ5D5L) at baseline (randomization), at 3 months, and 6 months. At 6 months after CRS-HIPEC, all patients undergo a follow-up of CT, MRI, serum biomarkers (carcinoembryonic antigen or CEA, cancer antigen 125 or CA 125, and cancer antigen 19.9 or CA 19.9), and physical examination to screen for early disease recurrence in the peritoneum, liver, or elsewhere. This will also serve as an extra quality check of diagnostic and surgical outcome. It is expected that a residual peritoneal or non-peritoneal metastasis will have become apparent at 6 months on MRI. If residual disease of early recurrence is observed, treatment is at the discretion of the local MDT. The trial schedule is summarized in Table 2.

**Table 2 Tab2:** Schedule of enrolment, interventions, and assessments

STUDY PERIOD						
	Enrolment	Allocation	Diagnostic Work-up	Treatment	Follow-up	
TIMEPOINT^b^	***-T***_***1***_	T_**0**_	T_**1**_	T_**1**_	***T***_***3***_	***T***_***6***_

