### Outcome measures

The primary outcome measure is a composite endpoint of futile surgical explorations. A futile surgical exploration is defined as: all surgeries in patients with definitely inoperable disease (PCI > 24) or explorative surgeries in patients with limited disease (PCI < 15).

The secondary outcomes include:
number of incomplete CRS-HIPECs (R2a/ R2b/ open-close),number of residual disease events or early recurrences at 6 months after a complete resection at CRS-HIPEC,number of non-peritoneal metastases,diagnostic performance of MRI and diagnostic laparoscopy to predict whether complete CRS-HIPEC is feasible,correlations between MRI findings and surgical findings,incremental cost-effectiveness,Patient reported QOL between study arms.

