### Statistical analysis

#### Sample size calculation

Power calculations are based on an expected reduction of futile surgical explorations from 30 to 15% by MRI staging. With a two-sample two-sided test of binomial proportions and an α of 0.05, a ß of 0.20, and an expected drop-out rate of 20%, 272 patients are to be included in total.

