### Data analysis

The observed difference in preventable surgical explorations between trial arms will be tested with a McNemar’s chi-squared test, as well as the difference in incomplete CRS-HIPECs, non-peritoneal findings before surgery, and early recurrences or residual disease visible at first follow-up (6 months). Progression free survival will be analyzed by binomial logical regression analysis. Progression free survival is defined as the time in days from complete CRS-HIPEC to recurrence or progression of disease as determined by the multidisciplinary team meeting or death of any cause. Correlations between MRI staging and surgical staging will be evaluated by intraclass correlation coefficients (ICC), Cohen’s kappa, and Cohen’s weighted kappa, where appropriate. Diagnostic performance of MRI and surgical staging to predict complete CRS will be compared by confusion matrix analysis and receiver operator characteristic analysis. Differences in predictive values will be tested with McNemar’s test and the DeLong test, where appropriate.

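### Progression-free survival is defined as a time in days but assigned to binomial (logistic) regression, with no fixed time point and no censoring rule

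*Protocol article*

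**What the plan says.** Two adjacent sentences in the Data analysis section of the protocol article deal with PFS. The first names the method: "Progression free survival will be analyzed by binomial logical regression analysis". The second gives the endpoint: "Progression free survival is defined as the time in days from complete CRS-HIPEC to recurrence or progression of disease". It leaves the call on recurrence or progression to the multidisciplinary team and also counts deaths, whatever their cause. Neither sentence attaches a time point to PFS, says how a patient without an event is treated, or names the groups or covariates to be compared.

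The same section has a separate yes/no outcome, recurrence or residual disease seen at the 6-month follow-up, and assigns it to McNemar's test. The Outcome measures section lists that outcome as "number of residual disease events or early recurrences at 6 months after a complete resection at CRS-HIPEC". PFS is not in that list.

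The only scheduled disease assessment after surgery is in Study interventions: "At 6 months after CRS-HIPEC, all patients undergo a follow-up of CT, MRI, serum biomarkers". Table 2 ends at the same visit.

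**The concern.** The endpoint is a duration that can be cut short by loss to follow-up or by the end of the study. The named model takes a binary response. To run it, someone must first turn the duration into event yes or no, and the protocol does not say how. Two choices follow, and neither is harmless:

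- **Which horizon.** Without a fixed time, the response becomes whether the patient was ever seen to progress. That depends on how long the patient was watched.
- **What to do with patients not followed to the horizon.** They must be excluded, which discards the event-free time they contributed, or counted as event-free, which understates the event rate.

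If these choices are left until the data are in, the reported odds ratio has no definition fixed in advance. If follow-up differs between the groups compared, the odds ratio can depart from 1 when the hazards are identical.

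**Working it through.** **Stated figures.** The protocol gives no PFS rate, hazard ratio, event count or power, so there is no figure to reproduce. All PFS rates below are assumptions.

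**Step 1: does the text allow a binary reading?** PFS is measured in days and counts death from any cause. The 6-month outcome is a count of recurrences or residual disease and has its own test. If PFS were that same outcome, a definition in days would serve no purpose. So PFS as written is a time-to-event variable paired with a binary model.

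**Step 2: loss of precision at the same horizon.** Assume exponential PFS with median m, everyone followed completely to time h, and an effect near the null. Let L = ln 2 × h/m and S = exp(−L). Information per patient on the log hazard ratio is:

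- from yes/no status: L² × S/(1 − S)
- from full event times: 1 − S

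With m = 12 months:

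- h = 6: L = 0.347, S = 0.707. Yes/no: 0.120 × 0.707/0.293 = 0.290. Event times: 0.293. Variance ratio 0.293/0.290 = 1.01, about 1% larger.
- h = 24: L = 1.386, S = 0.25. Yes/no: 1.922 × 0.25/0.75 = 0.641. Event times: 0.75. Variance ratio 0.75/0.641 = 1.17, about 17% larger.

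Range over the assumed median, using ratio = (1 − S)²/(L² × S):

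| Median (months) | Horizon 6 months | Horizon 24 months |
|---|---|---|
| 6 | 1.04 | 1.83 |
| 12 | 1.01 | 1.17 |
| 18 | 1.005 | 1.07 |

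**Step 3: the odds ratio moves with follow-up even when follow-up is equal.** Take an assumed constant hazard ratio of 0.65 and a comparison-group median of 12 months.

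- At 6 months the event-free proportions are 0.707 and 0.707^0.65 = 0.798. Odds ratio = (0.202/0.798)/(0.293/0.707) = 0.61.
- At 24 months they are 0.25 and 0.25^0.65 = 0.406. Odds ratio = (0.594/0.406)/(0.75/0.25) = 0.49.

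One treatment effect gives two odds ratios, according to a horizon that the protocol does not state.

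**Step 4: unequal follow-up.** A simulation of 3,000 runs assumed 80 patients per group, exponential PFS with a 12-month median and censoring uniform from 6 to 36 months. Censored patients were counted as event-free in the binary analysis.

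| Scenario | Log-rank rejects | Yes/no log odds ratio rejects |
|---|---|---|
| Hazard ratio 1, equal follow-up | 5.2% | 5.4% |
| Hazard ratio 1, follow-up 4 months shorter in one group | 5.1% | 19.7% |
| Hazard ratio 0.65, equal follow-up | 55% | 44% |

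In the second row the observed event proportions are 0.663 and 0.575, so the odds ratio is (0.575/0.425)/(0.663/0.337) = 0.69 with no true effect. In the third row the power gap corresponds to a variance ratio of about 1.3, because (1.96 + 0.13)²/(1.96 − 0.15)² = 4.37/3.28 ≈ 1.3.

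**The case against.** The best defence is that PFS may be meant to stop at the 6-month visit. That is the only scheduled disease assessment, it applies to all patients after CRS-HIPEC, and Table 2 ends there. Follow-up would then be nearly equal, and logistic regression of 6-month status would be defensible apart from dropouts. With one scheduled scan, many recurrences would also be dated at that scan, so event times would add little. The 1% figure at 6 months agrees with this.

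Part of this stands. It limits the harm, and it makes a fixed-time binary outcome a legitimate remedy. It does not rescue the text, which attaches no 6-month limit to PFS, defines it in days, and treats the 6-month outcome separately. Nor does an unseen analysis plan settle the matter, because the protocol names a method that does not fit rather than leaving it open.

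Three stronger readings are tempting, and the documents do not support them:

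- **A 2.5-fold loss of precision.** A reader might compare events by 24 months with events by 6 months: 0.75/0.293 = 2.56 under the 12-month median. That measures longer follow-up, not the choice of model. A Cox model stopped at 6 months would lose the same events.
- **Follow-up will be unequal, or will differ by arm.** The protocol gives a start in September 2019 and, for its sample size, an expected 20% drop-out. It does not say that PFS follow-up varies or differs between arms, and the PFS sentence names no arm contrast. The 19.7% error rate rests on an assumed 4-month gap; with equal follow-up the rate was 5.4%.
- **A key trial conclusion is at risk.** The sample size rests on futile explorations, and PFS is not in the outcome list.

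**Conclusion.** The mismatch between endpoint and method is real and is wrong as written. The named model cannot analyse the defined variable without a horizon and a rule for incomplete follow-up, and the protocol states neither.

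The size is moderate. With complete equal follow-up, the precision lost is negligible at 6 months and about 17% in variance at 24 months, under an exponential PFS with an assumed 12-month median. The larger problem is that the odds ratio depends on follow-up and is biased if follow-up differs between the groups compared. How far that happens here cannot be judged from the protocol. This should be fixed, but it does not bear on the primary analysis.

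One limit applies whichever model is used. PFS starts at complete CRS-HIPEC, and the staging strategy under test influences who reaches that point. An arm comparison in this subset is not a fully randomized comparison, and a survival model does not change that.

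**What to change.** Replace the PFS sentence with one of two consistent versions, before any comparative data are seen.

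1. **Keep PFS as a time.** Use Kaplan-Meier curves, with a log-rank test and a Cox model (hazard ratio with 95% confidence interval) stratified by center, as the randomization is. Censor patients without an event at the last disease assessment. Report 6-month PFS as the Kaplan-Meier estimate.
2. **Make it a yes/no outcome.** Redefine it as progression status (recurrence, progression or death) at a stated fixed time after complete CRS-HIPEC, say how patients not followed to that time are handled, and keep logistic regression.

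In either case, state that a comparison of arms among patients with complete CRS-HIPEC uses a post-randomization subset and should be read accordingly.

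The cost is a few sentences. The first version needs event dates and dates of last assessment; a definition in days already implies event dates. Follow-up beyond 6 months would need extra data collection only if PFS is meant to run past the last scheduled visit.

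### The planned accuracy comparison of MRI with laparoscopy uses differently selected, partly unverified patients, so equally accurate tests would differ, in a direction set by the patients analysed

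*Protocol article*

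**What the plan says.** All references are to the protocol article.

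- **Outcome measures** lists as a secondary outcome the "diagnostic performance of MRI and diagnostic laparoscopy to predict whether complete CRS-HIPEC is feasible".
- **Data analysis** fixes the comparison: "Diagnostic performance of MRI and surgical staging to predict complete CRS will be compared by confusion matrix analysis and receiver operator characteristic analysis". It adds: "Differences in predictive values will be tested with McNemar’s test and the DeLong test, where appropriate". It does not name the patients in whom each test is assessed.
- **Study interventions** gives the staging MRI to arm A. DLS in arm A is considered at MRI-PCI 15-24: "The MRI-PCI cut-off of 15 ensures targeted use of DLS". The MDT may also choose DLS for specific disease locations. Arm A patients with MRI-PCI above 24, or with non-peritoneal lesions that rule out CRS-HIPEC, go to chemotherapy or best supportive care.
- **Study interventions**, on arm B, leaves DLS to the MDT, decided before randomisation and with no common rule: "The rate of laparoscopy use may therefore vary between centers".
- **Data collection** makes surgical findings the reference standard.

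**The concern.** AUC and predictive values describe a test in a particular mix of patients. MRI is applied across arm A, including patients with clearly limited or clearly extensive disease. DLS in arm A is concentrated near the operability limit, where any test does worse. DLS in arm B is done in whomever local MDTs select. A difference between the two sets of figures therefore mixes test accuracy with referral policy.

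A second problem lies on top of this. The reference result comes from surgery, and the staging result helps decide who has surgery, so each test is verified in a group shaped by its own findings.

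The article concludes that the trial determines whether MRI can replace surgical staging, and its Discussion sets PPVs of MRI and DLS side by side. A confounded accuracy difference could be cited in support of replacement, or against it.

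**Working it through.** The plan gives no accuracy figure to reproduce, and its total of 272 is sized on the primary outcome. The check asks what the planned comparison would show if MRI and DLS were **equally accurate**.

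**Inputs from the protocol:** DLS band MRI-PCI 15-24; no surgery above MRI-PCI 24; eligibility limit PCI 20.

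**Assumptions (the protocol gives none of these):** true PCI is gamma with shape 2, scale 7 or shape 1.5, scale 8. Each test equals true PCI plus independent normal error, SD 3 or 5, the same for both tests. CRS is complete if PCI plus noise (SD 2) is at most 20. A test is positive for operability at 20 or below. There are 400,000 simulated patients per scenario.

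**Formulas:** AUC = P(a patient with complete CRS scores lower than one without). PPV = se × prev / [se × prev + (1 − sp) × (1 − prev)].

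**Step 1. Full reference results, gamma(2, 7), error SD 5**

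| Test and patients | prev | se | sp | AUC | PPV |
|---|---|---|---|---|---|
| MRI, all arm A | 0.775 | 0.918 | 0.817 | 0.952 | 0.945 |
| DLS, if done in everyone | 0.775 | 0.918 | 0.818 | 0.953 | 0.946 |
| DLS, MRI-PCI 15-24 | 0.702 | 0.803 | 0.683 | 0.831 | 0.856 |
| MRI, MRI-PCI 15-24 | 0.702 | 0.730 | 0.568 | 0.702 | 0.799 |
| DLS, arm B, higher-CT half | 0.587 | 0.856 | 0.836 | 0.930 | 0.881 |
| DLS, arm B, lower-CT half | 0.962 | 0.955 | 0.626 | 0.937 | 0.985 |

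PPV check, row 1: 0.918 × 0.775 = 0.711; 0.183 × 0.225 = 0.041; 0.711 / 0.752 = 0.945. Row 3: 0.803 × 0.702 = 0.564; 0.317 × 0.298 = 0.094; 0.564 / 0.658 = 0.857, which agrees to rounding.

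- *Unpaired, row 1 against row 3:* AUC 0.952 − 0.831 = 0.121 and PPV 0.945 − 0.856 = 0.089, towards MRI. Over the four scenarios the gaps are 0.12-0.14 and 0.09-0.12. A second model (gamma mean 10-14, SD 7-8, no noise on completeness) gives 0.08-0.10 and 0.05-0.08.
- *Paired arm A subset, row 4 against row 3:* AUC 0.702 − 0.831 = −0.129, **against** MRI. At error SD 3 it is 0.786 − 0.842 = −0.056. MRI has been restricted to its own middle range, so it discriminates less there.
- *Arm B, row 1 against rows 5 and 6:* in the higher-CT half, PPV leans to MRI (+0.064) and specificity to DLS (−0.019). In the lower-CT half, PPV leans to DLS (−0.040) and specificity to MRI (+0.191). If every arm B patient had DLS, this gap would be nil.

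**Step 2. Operated patients only.** Assume a band patient proceeds if DLS-PCI is at most 20. Then 18-24% of arm A has no reference result for complete CRS; MRI-PCI above 24 alone accounts for 12-16%. In the Step 1 scenario:

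- MRI in arm A falls to AUC 0.856 and specificity 0.326, with PPV 0.969. Against band DLS (0.742, PPV 0.856) the gap is +0.114 in AUC and +0.113 in PPV.
- In the paired subset, MRI has AUC 0.674 against 0.742 for DLS, but PPV 0.898 against 0.856. The two measures now point in opposite directions.
- Even if all of arm B had DLS (AUC 0.873, PPV 0.946), MRI would differ by −0.017 in AUC and +0.023 in PPV through verification alone.

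**Step 3. What restricting to a common stratum achieves.** Second model, mean 12, SD 8, error SD 4; DLS planned in the third with the highest CT-PCI; surgery follows DLS-PCI up to 24 in both arms. The false MRI-minus-DLS gap moves from about +0.08 (arm A MRI against DLS pooled over arms) to −0.02 in AUC, and from +0.08 to +0.03 in PPV. If arm A band patients proceed only at DLS-PCI 20 or below, the remaining gaps are 0.86 − 0.89 = −0.03 and 0.96 − 0.91 = +0.05. With full reference results the stratum comparison is unbiased by construction, so the residual is verification bias.

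**The case against.** **The analysis set may be defined in a document not shown.** This is one of seven secondary outcomes, and the tests are to be used only where appropriate. That limits the weight of the point. It does not remove it, because the difficulty arises from combining two things the article does state: how DLS is allocated, and that the two tests will be compared. McNemar's test needs both tests in the same patients. For staging, that means arm A patients who went on to DLS, where the AUC bias runs against MRI.

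**A reader might infer that MRI accuracy is measured in all arm A patients.** The documents do not support this. Patients whom MRI sends to no surgery lack the surgical reference, so the full-reference MRI figures in Step 1 cannot be observed in this trial. The selection effect remains without them: with MRI limited to MRI-PCI 24 or below, the second model still gives 0.045-0.08 in AUC and 0.06-0.08 in PPV against band DLS.

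**A reader might infer that the comparison always favours MRI.** This is not supported either. It holds for arm A MRI set unpaired against DLS after a borderline MRI. It reverses in AUC in the paired subset, and against arm B it depends on MDT selection for which no rule is given.

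**The proposed stratum may not be available.** The pre-randomisation DLS decision is mentioned for arm B, and Data collection does not list it. A decision taken before allocation must exist for both arms, but its recording in arm A is not established. This objection stands and shapes the fix.

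**Conclusion.** The point holds in a limited form. The stated comparison sets MRI and DLS side by side in patients selected by different routes and verified only in part, with nothing to offset either. Equally accurate tests would give different AUCs and predictive values. Under the assumptions above, with full reference results, the false AUC difference is about 0.08-0.14 towards MRI when arm A MRI is compared unpaired with borderline-MRI DLS, and about 0.06-0.13 against MRI in the paired arm A subset. It is of undetermined sign against arm B. Because the sign changes with the analysis set, that set should be fixed before the data are seen.

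The simulations show mechanism and range, not a forecast; every size depends on assumed PCI distributions, test errors and referral rules. The randomised primary comparison is not touched.

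**What to change.** 1. Record the pre-randomisation DLS decision for every patient in both arms, and confirm that it was captured in arm A for patients already enrolled.
2. Make the main accuracy comparison MRI (arm A) against DLS (arm B) within the stratum where DLS had been planned, using methods for independent samples in place of McNemar's test and paired DeLong.
3. Do not pool arm A DLS into the DLS accuracy estimate. Report it separately as DLS after a borderline MRI.
4. Report MRI accuracy in arm A overall as descriptive.
5. State how patients without a surgical reference are handled, for example by a sensitivity analysis over their possible outcomes. Restricting the population does not remove partial-verification bias (Step 3).

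**Cost:** an analysis-plan change and possibly one data item, plus lost precision. With 272 patients, equal allocation (assumed) and 20% drop-out, about 272 / 2 × 0.8 ≈ 109 per arm remain. If DLS was planned in a third to a half, the stratum holds about 36 to 54 per arm, fewer once unverified patients are set aside. Intervals will be wide, which is acceptable for a secondary outcome.

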### Cost-effectiveness analysis

A cost-effectiveness Analysis will be performed with incremental costs per Quality Adjusted Life Year gained as outcome for patients with PM undergoing MRI versus usual diagnostic work-up for selection for CRS-HIPEC. A Markov model will be constructed, a lifelong time horizon with 3 months cycle length will be used, and a societal perspective from the Netherlands will be adopted. Future costs and effects will be discounted to their present value by a rate of 4 and 1.5% per year respectively, according to Dutch guidelines [25]. The results of the probabilistic sensitivity analysis will be illustrated in a cost-effectiveness plane, and cost-effectiveness acceptability curves (CEACs) will show decision uncertainty. CEACs show the probability that a pathway has the highest net monetary benefit, and thus is deemed cost-effective, for a range of Willingness to Pay values for one additional QALY, also referred as the ceiling ratio. In this analysis, we will use the Dutch (informal) ceiling ratio of €80,000 per QALY [26].

## Discussion

Selected CRC patients with limited PM can benefit from CRS-HIPEC with a chance of a significantly prolonged survival and in some cases even cure. Currently, the final clinical decision of whether complete resection at CRS-HIPEC is feasible is often determined during surgery. Rehabilitation from open-close surgery is not in the best interest of a palliative patient and may delay palliative treatment or inclusion in trials. Two trials are ongoing in the Netherlands exploring novel palliative strategies for patients with extensive CRCPM, namely the use of concomitant intraperitoneal and systemic chemotherapy (INTERACT) and repetitive electrostatic pressurized intraperitoneal aerosol chemotherapy with oxaliplatin (ePIPAC) [27, 28].

Twenty-three percent of candidates for the PRODIGE-7 trial were excluded at laparotomy due to the extent of PM, liver metastases or non-resectable disease [11]. Other studies have reported incomplete CRS rates of around 20–40%, when selecting patients suitable for CRS-HIPEC with CT [6, 7, 10]. To help reduce the incomplete CRS rate, laparoscopy can be used to better assess the feasibility of complete cytoreduction. Improvements of 7–15% in the number of incomplete CRS-HIPECs have been reported after clinical implementation of laparoscopy [10, 29]. A cohort study researching the clinical impact of implementing DLS into the diagnostic work-up reported that in 35.2% not all abdominopelvic regions were visualized at DLS [10]. PPVs for predicting complete cytoreduction have been reported of 0.63–0.97 with DLS [6, 8–10, 30]. Sensitivities and specificities of 0.80–0.98 and 0.85–0.93 have been reported with use of MRI at region-wise analysis in two cohort studies of 27 and 60 patients [17, 18], from with a PPV of 0.90 could be achieved for predicting an operable extent of disease [17]. This was in concordance with the findings of Van’t Sant and colleagues who reported a PPV of 0.89 finding an operable extent of disease in a cohort study of 49 patients [15]. MRI can give information about peritoneal involvement in all regions, even those that might not be accessible with DLS due to adhesions, tumor, or anatomical limitations (such as diaphragmatic dorsal area and gastrosplenic ligament). MRI staging may therefore aid operative planning. MRI is furthermore non-invasive and much less costly than a diagnostic laparoscopy.

A limitation of MRI in the work up of CRC patients with PM is the lack of histopathological proof of identified lesions. However, we expect that in most cases patients will have lesions that are accessible by biopsy or present with proven PM during a previous surgical procedure. If this is not the case, a DLS may still be necessary. Patients with severe claustrophobia as well as patients with metal implants non-compatible with MRI are not eligible for MRI assessment. Policy differences between hospitals may lead to differences in laparoscopy rates and open-close rates in the control arm. Assuming that the rate of DLS is inversely related to the incomplete and open-close rate, the potential benefit of additional MRI staging could nonetheless become apparent. Furthermore, the benefit of Oxaliplatin-based HIPEC in the combined CRS-HIPEC procedure has recently come under debate following the results of the PRODIGE-7 trial [11]. However, this study reinforced the notion that complete cytoreduction is the most determinant factor of survival, a finding that underlines how important it is to safely and effectively select those patients for whom a complete CRS is feasible. Therefor our trial would continue to be relevant to select patients for CRS, alone or CRS in combination with any perioperative therapy.

If MRI staging effectively reduces the number of surgical explorations in CRS-HIPEC candidates, patients with PM from CRC will be exposed to a less invasive and more effective triaging system.

